### Recruitment {15}

Medical centers known to conduct a substantial volume of LAAC procedures were invited to participate in the study. Among individuals referred to these centers, patients eligible to participate in the study will be selected based on the inclusion and exclusion criteria.

## Assignment of interventions: allocation

### Sequence generation {16a}

Block randomization will be employed to uphold the proportional allocation of subjects across the two groups. The blocks will consist of four subjects each. Randomization will be centrally executed to mitigate the foreseeability of the forthcoming treatment modality for successive patients. This will be accomplished by utilizing existing computer algorithms facilitated by the Interactive Web Response System.

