### Trial design {8}

The LAAC-SBI trial is designed as a prospective, multicentre, randomized, and double-blind interventional study. Its primary objective is to recruit a total of 240 patients, with an equal allocation of 120 patients to each group. The study group will examine the effectiveness of utilizing the Sentinel CPS during LAAC procedures, whereas the control group will undergo LAAC without using the Sentinel CPS (Fig. 1). The study was designed to demonstrate the superiority of an experimental procedure, i.e. the use of Sentinel CPS during LAAC, over a control intervention.

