## Methods: participants, interventions, and outcomes

### Study setting {9}

This study is being started by an academic hospital. The study intends to involve eight centers located in Poland. You may find a current and complete list of these collaborating hospitals on ClinicalTrials.gov.

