### Sample size {14}

Based on the assumptions that cerebral protection during LAAC would result in a favorable response in 85% of patients and that the absence of new SBI on DW MRI in the control group would affect 70% of patients, the minimum group size was estimated to be 118 individuals per group. This estimation ensured 80% power to detect the anticipated difference at a significance level of 5%. Considering a withdrawal or invalidation ratio of 2%, a total of 120 individuals will be enrolled in each group, resulting in a sample size of 240 patients for the study. This sample size is necessary to provide sufficient statistical power and enable meaningful comparisons between the study and control groups.

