### Implementation {16c}

Unblinded researchers will enroll patients at each participating medical center based on predetermined inclusion and exclusion criteria. Additionally, these researchers will carry out patient randomization utilizing a central computer system. External monitors to the study sponsor will oversee the accuracy of patient inclusion and adherence to the randomized assignments. These monitors are affiliated with the BioStat Sp. z o.o., a Clinical Research Organization (CRO) specializing in comprehensive research services. The study Sponsor has established a contractual agreement with this CRO for these monitoring purposes.

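### A published, fixed block size of four, with unblinded site staff who both enrol and randomise, leaves allocation foreseeable if blocks run within centre

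*Protocol article*

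**What the plan says.** All references are to the protocol article.

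- **Sequence generation {16a}:** "Block randomization will be employed to uphold the proportional allocation of subjects across the two groups". The size is fixed: "The blocks will consist of four subjects each". The stated safeguard is central execution by an Interactive Web Response System (IWRS): "Randomization will be centrally executed to mitigate the foreseeability of the forthcoming treatment modality for successive patients". No stratification factor is named.
- **Implementation {16c}:** "Unblinded researchers will enroll patients at each participating medical center based on predetermined inclusion and exclusion criteria". The same section adds that "these researchers will carry out patient randomization utilizing a central computer system".
- **Who will be blinded {17a}** and **Concealment mechanism {16b}:** blinding covers the patient, the examining neurologist and the central radiologist. It does not cover the staff who recruit.
- **Study setting {9}:** "The study intends to involve eight centers located in Poland".
- **Trial design {8}:** the aim is to "recruit a total of 240 patients, with an equal allocation of 120 patients to each group".
- **Trial status:** recruitment began on 26 May 2023 and was expected to finish by September 2025.

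**The concern.** The plan names foreseeability as something to prevent and relies on central execution to prevent it. That protects the list itself, but not against deduction. A recruiter who sees each allocation and knows that every block holds two of each arm can tell the last place in a block, and sometimes the last two, provided the block belongs to that centre.

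The Eligibility criteria {10} leave room for judgement at entry, for example on anatomical obstacles and on contraindications to anticoagulants. Someone who knows the next arm could defer or decline a patient. Blinded reading of the MRI and blinded cognitive testing guard against biased assessment. They cannot undo selection that took place before randomisation.

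If there is instead one list for all centres, deduction at a site largely fails, but nothing in the scheme keeps the arms balanced within a centre.

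**Working it through.** **The plan's own figure.** The randomisation sections give no numerical result. The total of 240 comes from Sample size {14}, which assumes 85% against 70%, 80% power and a 5% level (taken as two-sided). The unpooled formula gives (1.960 + 0.842)² × (0.85 × 0.15 + 0.70 × 0.30) / 0.15² = 7.849 × 0.3375 / 0.0225 = 117.7, so 118 per group as stated. The present point does not depend on this.

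**Inputs from the article.** Block size 4, allocation 1:1, 240 patients, 8 centres. **Assumption:** centre sizes, which are not given, so a range is shown.

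**Case A: blocks run within centre**

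There are 4!/(2!2!) = 6 possible blocks. The observer knows the block size and the earlier allocations at the centre.

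| Place in block | Known with certainty | Best guess correct |
|---|---|---|
| 1 | 0 | 1/2 |
| 2 | 0 | 2/3 |
| 3 | 1/3 (when the first two match) | 1/3 × 1 + 2/3 × 1/2 = 2/3 |
| 4 | 1 | 1 |
| Sum | 4/3 | 17/6 |

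- Certain: (4/3)/4 = 33.3%. Over 240 patients in complete blocks, 240/3 = 80.
- Best guess: (17/6)/4 = 70.8%, against 50% with no information.
- With 30 patients per centre there are seven full blocks and two further patients, neither of whom is certain. Certain allocations are 8 × 7 × 4/3 = 74.7, about 75. The best-guess rate is (7 × 17/6 + 1/2 + 2/3)/30 = 21/30 = 70.0%.

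Hence about 75 to 80 certain allocations and a guess rate of about 70–71%.

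**Case B: one central list of blocks of four**

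This was simulated with 240 patients over eight centres. Each site sees only its own past allocations and guesses the arm that is behind.

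- A site guesses right about 51% of the time.
- The mean absolute arm difference per centre is about 4 patients, and the mean of the largest across the eight centres is about 9.
- Probability that at least one centre has an arm difference of 8 or more (19:11 in a centre of 30):

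| Assumed centre sizes | Probability |
|---|---|
| Unequal: 30/20/15/10/10/5/5/5% of patients | about 63% |
| Equal in expectation, actual sizes left to chance | about 68% |
| Exactly 30 in every centre | about 75% |

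**What varying the block size does**

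- Within centre, with 30 patients each, guessing the arm that is behind is right about 70% of the time with fixed fours, 69% with a random mix of 4 and 6, and 67% with a mix of 4, 6 and 8. The guess rate falls little. The gain is that block ends are no longer known, so most of the certainty goes.
- On a single list, a mix of 4, 6 and 8 leaves the site guess rate at about 51%.
- Moving from a single list to within-centre blocks of 4, 6 and 8 would raise the guess rate from about 51% to about 67%.

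**The case against.** The strongest reply is that neither harm is established. The two exclude each other, and the article does not say which scheme applies. Sequence generation {16a} names no strata and stresses central execution, which reads at least as naturally as a single list, and then the one-third and 71% figures do not apply. This stands: the predictability figures are conditional.

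A reader might infer that the trial lacks centre stratification or a centre term in its analysis. The documents do not support that. A condensed article commonly leaves both to the full protocol or analysis plan, and Statistical methods {20a} names ANCOVA without listing covariates, so a centre factor is not excluded.

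A reader might also infer that centre imbalance on a single list would confound operator with device. It would be chance imbalance, which costs precision without biasing the comparison. No section gives data on how the outcome varies by operator or centre.

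There are also safeguards: eligibility criteria are set in advance, and external monitors check inclusion and adherence to the assignment (Implementation {16c}). They make selective entry harder but do not remove foreknowledge.

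What the reply does not remove is that the fixed size and the unblinded recruiter role are stated outright. They are not gaps left by condensation, and further detail elsewhere would not undo the disclosure.

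**Conclusion.** The point holds in conditional form. A fixed, published block size of four, used by unblinded staff who both enrol and randomise, means that central execution alone does not secure the plan's aim of limiting foreseeability.

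- **If blocks run within centre:** about 75 to 80 of 240 allocations are certain in advance and the best guess is right about 70–71% of the time. This assumes that recruiters know the block size and keep track of local allocations.
- **If there is one list:** local guessing is near chance at about 51%, assuming that a site sees only its own allocations. What remains is a loss of precision from chance imbalance across centres, with a range of 63–75% that depends on assumed centre sizes.

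The documents do not show that any allocation was predicted or any patient selected on that basis. Nor do they give the article's publication date or the number of patients still to be randomised, so how much of recruitment a change could still affect is unknown.

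**What to change.** 1. For the remaining patients, replace the fixed block of four with block sizes that vary at random (for example 4, 6 and 8), and keep the values out of site-facing and public documents.
2. Keep whichever scheme is in use. Do not move a single central list to within-centre blocks for this purpose, because that would make guessing easier.
3. Include centre as a factor or stratum in the primary analysis, if the analysis plan does not already do so. This can still be done if recruitment has ended.

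**Cost:** a small IWRS change, and notice of the amendment to the Ethics Committee and the registry as the section on communicating amendments {25} requires. Arm totals may differ by a few patients: with blocks of 4, 6 and 8, by at most 4 on a single list, and by about 2 on average (6 or fewer in about 95% of simulated trials) within eight centres of 30.

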### Concealment mechanism {16b}

The Sentinel CPS is introduced via a radial artery access and is preceded by aortography. To minimize subjectivity during patient evaluations of at follow-up visits, individuals within the control group will similarly undergo arterial puncture and aortography, mimicking the setup process for the Sentinel CPS. Furthermore, the neurologist conducting the neurological examination, utilizing the NIHSS score and cognitive functionality assessments, will be kept unaware of the patient’s allocation to either study arm. They will also not have access to the eCRF to prevent any knowledge about the patient’s assignment to the study or control group. This approach, known as “investigator blinding,” aims to ensure impartial evaluation.

### Implementation {16c}

Unblinded researchers will enroll patients at each participating medical center based on predetermined inclusion and exclusion criteria. Additionally, these researchers will carry out patient randomization utilizing a central computer system. External monitors to the study sponsor will oversee the accuracy of patient inclusion and adherence to the randomized assignments. These monitors are affiliated with the BioStat Sp. z o.o., a Clinical Research Organization (CRO) specializing in comprehensive research services. The study Sponsor has established a contractual agreement with this CRO for these monitoring purposes.

## Assignment of interventions: blinding

### Who will be blinded {17a}

Both the patient undergoing assessment and the neurologist conducting the physical examination and cognitive tests will be kept uninformed regarding the utilization of neuroprotection with the Sentinel CPS during the LAAC procedure. Furthermore, DWI MRI images will be evaluated at a central laboratory separate from the centers participating in the study. The radiologist responsible for analyzing the DWI MRI images will also remain unaware whether the patient was assigned to the study or control groups. This approach ensures an unbiased and impartial assessment of outcomes.

### Procedure for unblinding if needed {17b}

Given that the Sentinel CPS is employed to prevent perioperative stroke, details concerning its utilization remain independent of managing potential perioperative complications or the emergence of new medical conditions during the follow-up period. Consequently, it is anticipated that no unblinding procedures will be implemented throughout the study.

## Data collection and management

### Plans for assessment and collection of outcomes {18a}

For the study, researchers must possess a valid Good Clinical Practice certificate. To acquire robust data regarding the efficacy of neuroprotection during LAAC procedures and to evaluate the clinical advantages of employing the Sentinel CPS, both imaging data—specifically brain DWI MRI—and assessments of cognitive functions and mood disorders will be collected. To ensure the accuracy of DWI MRI data, these images will undergo analysis at a central laboratory. Additionally, detailed instructions regarding the DWI MRI protocol will be furnished to participating centers.

Conversely, the evaluation of cognitive functions and mood disorders will involve the utilization of validated questionnaires. The use of these questionnaires is authorized by entities holding the respective copyrights. Researchers tasked with administering the Montreal Cognitive Assessment (MoCA) test must hold certification for conducting and interpreting the test. This certification is granted after completing appropriate training, available at mocacognition.com.

### Plans to promote participant retention and complete follow-up {18b}

To ensure participants’ continued engagement in the study, a telephone reminder will be implemented before the upcoming follow-up visit. If a participant becomes unable to attend follow-up visits due to health-related or other reasons (excluding withdrawal of informed consent), the researcher will make diligent attempts to document the observation comprehensively. This will involve initiating telephone correspondence with the participant, contacting their family, or liaising with their healthcare provider or relevant institution/authority. These measures are intended to facilitate remote interviews and accurately assess the participant’s condition.

### Data management {19}

A data management plan version 1.0 has been prepared, the purpose of which is to present the procedures and control mechanisms necessary to ensure the protection, authenticity, confidentiality, completeness, and integrity of data collected from study participants, as well as the mechanisms necessary to ensure that the clinical database created as part of the study will be complete, cleaned and usable for the Sponsor and statisticians to analyze the collected data and prepare the clinical trial report. This document has been prepared in accordance with the guidelines of “Good Clinical Data Management Practices” and the regulations of 21 CFR Part 11. This document will be updated throughout the study to reflect changes to the electronic Case Report Form (eCRF) and comments from Monitors, Sponsor, Investigators, and Coordinators. Clinical data for the LAAC-SBI study is collected through the eCRF.bizTM system, an Electronic Data Capture platform developed by BioStat. This system is fully validated and serves as the repository for study-related information. The eCRF.bizTM system operates on a server running the GNU/Linux Debian 11 operating system. It utilizes PHP version 7.2.34, MySQL database version 8.0.29–2, and Apache web server version 2.4.54. Certain functionalities linked to reporting and encoding medical data involve using the R statistical software (version 3.3 or later) and the Python programming language (version 3.5). To ensure security, the system has been situated on a secure server hosted at the data center of OVH, a prominent European service provider known for its reliable infrastructure.

### Confidentiality {27}

All patient data entered into the eCRF are anonymous and identifiable by a unique patient number generated when creating the patient card. The research team is responsible for keeping information about the patient’s assigned number in the records kept at the site.

### Plans for collection, laboratory evaluation, and storage of biological specimens for genetic or molecular analysis in this trial/future use {33}

The current study does not plan to obtain biological material for genetic and molecular research.

## Statistical methods

### Statistical methods for primary and secondary outcomes {20a}

The primary analysis of all endpoints will be conducted using an intention-to-treat approach, wherein participants will be analyzed according to their initial randomization assignment, irrespective of the actual treatment received. Quantitative variables will be presented as either mean or median values, while qualitative variables will be reported as counts (with percentages). To assess the distribution of quantitative variables, the skewness index will be employed. Between-group comparisons will be carried out using independent *t*-tests and ANCOVA for quantitative variables. A chi-square test will be used to compare distributions between the two groups for qualitative variables.

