The most extensive multicenter and prospective study, SENTINEL-H, involved 217 patients undergoing TAVI. Using the Sentinel CPS device was associated with minimal risk to patients, as indicated by the high success rate of device insertion and removal (94.4%) and only one case (0.4%) of access site vascular injury. Strokes occurred in 5.6% of patients treated with the Sentinel CPS, compared to 9.1% in the control group. Among patients who experienced a stroke, the size and number of DW-MRI lesions were reduced when the Sentinel CPS was employed. The study revealed a correlation between SBI volume and cognitive decline (*r* =  − 0.25; *p* = 0.002 for protected areas); however, the differences between the study and control groups were not statistically significant. The study’s authors attributed this finding to significantly reduced cognitive functions at the study’s baseline [15].

In the DEFLECT III study, which included 85 randomized patients, the TriGuard system was compared to no neuroprotection during TAVI. The use of the TriGuard system was associated with a higher rate of no new SBI occurrences (26.9% vs. 11.5%), a lower incidence of neurological deficits assessed by the National Institutes of Health Stroke Score (NIHSS) (3.1% vs. 15.4%), and better outcomes on the Montreal Cognitive Assessment (MoCA) test. Additionally, patients using the TriGuard system were twice as likely to experience cognitive function normalization in the MoCA test after 30 days (45.5% vs. 20%; RR 2.27 [95% CI 1.01, 5.1]) [16].

The Sentinel CPS has received approval to prevent embolism by capturing and removing embolic materials, such as clots or fragments, that may enter the cerebral vasculature during endovascular procedures. However, it should be noted that the embolic material encountered during TAVI procedures differs from the embolic material found in the left atrial appendage (LAA) in structure, quantity, and nature. No randomized trials have been conducted to specifically assess the impact of using neuroprotective devices during LAAC. Only isolated cases of utilizing such devices during LAAC procedures have been described. The largest reported sample includes six patients with a thrombus present in the LAA, in whom the implementation of brain protection devices prevented the occurrence of overt stroke. However, cognitive function assessments were not conducted before and after the procedure, and no brain imaging studies were performed [17].

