### Criteria for discontinuing or modifying allocated interventions {11b}

Analyses within the study will be carried out in accordance with the principle of intent-to-treat. Consequently, should a participant assigned to the study group not receive the Sentinel CPS intervention, they will still be retained within the study group. There will be no reassignment of participants between the study and control groups.

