### Methods in analysis to handle protocol non-adherence and any statistical methods to handle missing data {20c}

Instances where the procedure is not conducted per protocol, must be documented along with the underlying reasons. The analysis will still include data regarding the study participants who did not undergo the procedure aligned with their randomized group. The CRO and the Sponsor will regularly review the Protocol Deviation Reports. Should repeated deviations from the study protocol occur, the Sponsor reserves the authority to suspend recruitment at a particular center based on their judgment and decision-making.

Multiple imputations will be employed to address these gaps when data is missing for the independent (explanatory) variables. This method estimates the missing values based on the observed data, ensuring a more complete dataset for analysis. Conversely, for the dependent (outcome) variable, cases with missing data will be removed (using listwise/case deletion). The analysis will then be conducted solely on the remaining complete cases, utilizing the observed values of the outcome variable. This approach aims to maintain the integrity of the analysis while accounting for missing data in a systematic manner.

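### The all-endpoints intention-to-treat rule does not fit the two device-dependent secondary endpoints, filter debris and device complications

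*Protocol article*

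**What the plan says.** Statistical methods {20a} states one rule: "The primary analysis of all endpoints will be conducted using an intention-to-treat approach", with patients analysed as randomised "irrespective of the actual treatment received". No endpoint is exempted. For categorical outcomes the section provides counts with percentages and one test: "A chi-square test will be used to compare distributions between the two groups for qualitative variables".

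Two other sections carry the rule through. Under Criteria for discontinuing or modifying allocated interventions {11b}, "should a participant assigned to the study group not receive the Sentinel CPS intervention, they will still be retained within the study group". Under the non-adherence and missing-data section {20c}, "The analysis will still include data regarding the study participants who did not undergo the procedure aligned with their randomized group". For a missing outcome, however, the same section says that "cases with missing data will be removed (using listwise/case deletion").

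Outcomes {12} lists six secondary endpoints. Four (lesion volume, cognition, dementia, depressive disorders) can be measured in any patient. The other two are debris found in the device's filters and complications of using the neuroprotection system. The Concealment mechanism section {16b} adds that "individuals within the control group will similarly undergo arterial puncture and aortography", as a sham for device set-up.

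**The concern.** Intention-to-treat is the right principle for endpoints that every randomised patient can experience. It fits poorly where the endpoint presupposes the device. How often the filter catches material is a question about patients who had a filter. How often the device causes harm is a question about patients in whom insertion was tried. A denominator of everyone allocated to the device answers neither.

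For a harm endpoint the error runs in the unwelcome direction: patients never exposed make the device look safer. A control patient given the device by mistake would also have any device complication recorded under control. The between-arm comparison has a separate difficulty. Both arms undergo arterial puncture and aortography. If the endpoint is read as strictly device-attributed, the same access injury would count in the study arm and not in the control arm.

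The trial proposes adding an invasive step to LAAC, and its Discussion anticipates influencing guidelines, so the device-harm rate needs a defensible denominator and comparator.

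**Working it through.** **Denominator.** Sample size {14} gives 120 per group. Its base figure reproduces with unpooled variance, two-sided 5% and 80% power: (1.960 + 0.842)² × (0.70 × 0.30 + 0.85 × 0.15) / 0.15² = 117.7, so 118. Then 118 / 0.98 = 120.4, against 120 stated. The sample size is not at issue; only the 120 is used below.

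**Debris, between arms.** There are two ways to treat a patient with no filter.

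- Scored negative: controls without a filter are 0 of 120 by construction. With 4 of 120 in the study arm, the uncorrected chi-square is 240 × (4 × 120 − 0 × 116)² / (120 × 120 × 4 × 236) = 4.07, p = 0.044. With continuity correction p = 0.13, and by Fisher's exact test p = 0.12. At 6 of 120 against 0, all three fall below 0.05 (0.013, 0.039, 0.029). Such a result would show only that filters were present in one arm.
- Treated as unobserved and deleted under {20c}: the study denominator becomes patients with filters, but every control without a filter is deleted too, and no comparator remains.

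Neither reading gives an informative test. {20c} retains non-adherent patients and also deletes missing outcomes, so the text does not settle which reading applies.

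**Dilution.** Reported rate = rate among those exposed × (number exposed / 120). For harm, exposed means insertion was attempted. For debris, it means a filter was deployed, and the formula applies only if unfiltered patients are scored negative. The trial's non-exposure share is not given. The shares below and the true rates of 5% (harm) and 80% (debris) are assumptions.

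| Share not exposed | Number exposed | True 5% harm reads | True 80% debris reads |
|---|---|---|---|
| 5% | 114 | 4.75% | 76% |
| 10% | 108 | 4.5% | 72% |

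The relative reduction equals the share not exposed. With zero events, the one-sided 95% upper bound, 1 − 0.05^(1/n), is 2.5% on 120 and 2.7% on 108.

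**The cited device figures.** The Rationale reports 94.4% success of insertion and removal in the largest cited TAVI trial of this device. Taken as a receipt rate, it would leave 120 × 0.056 = 6.7 patients without the device. At 113 of 120, a 5% harm rate reads 4.7% and an 80% debris rate reads 75.3%. The figure combines insertion with removal, so it does not give the share with no filter. It gives no share with no attempt either, because a failed attempt is still exposure.

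**Access injury counted in one arm.** The Rationale gives 0.4% access-site vascular injury. At that rate 120 × 0.004 = 0.48 patients per arm. On the strict reading, about half a patient would be expected to count in the study arm and none in the control arm.

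**The case against.** The strongest reply is that the sentence fixes only the primary analysis. An as-treated or safety-set analysis could sit in an analysis plan that is not shown, and an article condenses its protocol. That is a fair answer to any complaint of omission. It does not answer this point, which concerns what the article does state: all endpoints, without exception. An as-treated device-safety analysis elsewhere would be supplementary to that text or would contradict it.

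Other objections stand and limit the point:

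- A reader might infer that the control arm is zero by definition for both endpoints. The documents support this only for debris in controls without a filter. Controls have the sham puncture and aortography, and the Rationale presents access-site injury as a risk of the device, so a broader reading of the complications endpoint admits control events.
- A reader might infer that debris capture is certainly diluted. It is not, if unfiltered patients are deleted as missing.
- A reader might take the whole 5.6% shortfall from 94.4% as harm dilution. Failed attempts were exposed to device risk and belong in the denominator; only patients with no attempt dilute the harm rate.
- A reader might expect a spurious gap of several percentage points in access harm. The only rate in the document, 0.4%, does not support that.
- Eligibility criteria {10} exclude anatomical obstacles to filter insertion, and monitors oversee adherence to assignment {16c}. Both argue against large non-receipt.
- Adverse event reporting {22} is not confined to the study arm, so serious access harm in controls would still be captured as a serious adverse event, though not necessarily in this endpoint.
- The chi-square sentence is generic and does not name these endpoints; counts with percentages would suit both. It is, however, the only between-group test given for qualitative variables.

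**Conclusion.** The point holds as a small, real flaw in a stated rule. Applied as written, the rule gives an uninformative between-arm comparison for filter debris, an unsettled debris denominator, and a device-harm rate that includes patients never exposed. Whether access injury is counted unequally depends on how the complications endpoint is read, and the text does not say.

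The size cannot be established, because the article gives no expected share of patients without an attempt or without a filter. If that share is 5% to 10% (assumption), the harm rate is understated by 5% to 10% relative; the same applies to debris if unfiltered patients are scored negative. On a 5% harm rate that is a quarter to half a percentage point. The primary MRI endpoint, the sample size and the other four secondary endpoints are unaffected. The correction is worth making because it is cheap and concerns device safety.

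**What to change.** In Statistical methods {20a}, exempt the two device-dependent endpoints from the all-endpoints intention-to-treat sentence and state:

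1. Filter debris is reported descriptively among patients in whom filters were deployed, with no between-arm test.
2. Device-related complications are reported descriptively among all patients in whom insertion was attempted, including failed attempts, by device actually used.
3. Any between-arm safety comparison uses procedural access, arch-vessel and cerebrovascular complications, defined identically in both arms and analysed as randomised. The control arm's sham puncture and aortography make the access part of this like-for-like.

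Intention-to-treat stays for the MRI, cognitive, dementia and mood endpoints. The cost is revised wording, slightly more analysis work and an eCRF category for access and arch complications in both arms. No extra patients or procedures are needed. The downside is that the reported device complication rate may look slightly less favourable.
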